### RCT overview

In this study, we will conduct an educational intervention as Black, Hispanic, and White ESRD patients present for and undergo transplant evaluation, and take actions to pursue DDKT and LDKT. This longitudinal, parallel RCT has two treatment conditions with equal allocation, the YPT Intervention and the UC control education conditions (Figure 2). Patients in both groups will be surveyed prior to presenting at the transplant center (baseline), and at 4- and 8-months post-baseline. Patients in the intervention group will also be surveyed an additional time during their in-person transplant evaluation meeting. Completion of transplant evaluation and receipt of LDKT will be assessed for both groups using medical records 18-months post-baseline.

**Figure 2 Fig2:**
[figure not shown]
**Your Path to Transplant study design flowchart.**

Patients in the YPT and UC education conditions will receive identical UCLA-KPTP education during transplant evaluation for an estimated 3 hours and will continue to learn on their own afterwards. Patients in the YPT intervention group also will receive additional sources of transplant education including individualized feedback reports, print and video education resources, and coaching at four time points: a few weeks before and during transplant evaluation, and 4 and 8 months after baseline. Patients in the intervention (YPT) condition will receive an estimated 1 hour and 15 minutes of additional formal transplant education compared to patients in the UC condition over an 8 month period.

### Patient recruitment, eligibility, randomization, and retention

The records of patients who have recently been scheduled for their evaluation day appointments will be obtained from UCLA-KPTP’s clinical database, randomized to a treatment group by a data manager, and uploaded into a patient recruitment and tracking database supported by the Research Electronic Data Capture (REDCap) software [46]. Research staff will contact patients by telephone to be invited to participate in the study. The REDCap recruitment database will include eligible patients’ names, contact information, demographic data, data on their retention in the study and progress through the survey time points, and their final clinical outcomes at the end of the trial. It will be continually updated by the study research coordinators and a data manager.

Inclusion criteria for the RCT include: 1) presentation for transplant evaluation at UCLA by calling to make an appointment; and 2) self-identification as either White, Black or Hispanic race/ethnicity. Exclusion criteria include: 1) being under age 18; 2) not being able to speak English; 3) being previously deemed ineligible for transplant at UCLA; 4) being on the wait-list for transplant at a center other than UCLA; 5) pursuing multi-organ transplant; or 6) having no consistent access to a working telephone. After being informed of the risks and benefits of the trial, patients will be asked to give verbal informed consent to participate and have their electronic medical records reviewed. This protocol has been approved by the University of California, Los Angeles’s Internal Review Board (#14-000382) and registered at ClinicalTrials.gov (#NCT02181114).

We will recruit 900 patients at baseline, 450 per treatment group. We estimate a conservative attrition rate of approximately 33%, resulting in a final sample of approximately 600 subjects, 300 in each group. To maximize participation and minimize attrition, we will provide a $10 incentive upon completion of each of the 3 or 4 time points (depending on treatment group), pay for the costs of transplant center parking and provide snacks at evaluation day, and collect alternative contact information at baseline in case of study dropout. We also have the ability to monitor patients’ progress through transplant evaluation daily using electronic medical records, which will greatly reduce the number of patients who are lost to follow-up.

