### Statistical analyses

All statistical tests will employ an intent-to-treat (ITT) approach wherein subjects will maintain their assignment to the treatment condition to which they were originally randomized regardless of whether they actually end-up receiving the planned interventions or not [56]. Multiple imputation of missing data will be used for the analyses [57]. The alpha level for all tests will be set at 0.05, and random effects models will be used to account for longitudinal measurement and linear regression employed for normally distributed outcomes, logistic regression for binomially distributed outcomes, and Poisson regression for count outcomes. The social, demographic, and other characteristics of patients who refuse to join the study or are never successfully contacted will be compared to those who do not to determine if the patient selection procedure has resulted in a biased sample. A similar analysis will be conducted to compare the patients who drop-out of the study to those who do not to determine if patient attrition has biased the sample.

To test whether, compared to the UC education condition, Black, Hispanic, and White patients receiving YPT increase in their LDKT readiness, we will first examine the proportion of individuals moving into the Action stage for readiness to accept a LDKT 8 months post-baseline between the YPT and UC conditions. For a more fine grained assessment of change in LDKT and DDKT readiness throughout the study, change by three occasions (baseline, 4 months post-baseline, and 8 months post-baseline) will be examined. To assess differences in transplant knowledge, DDKT/LDKT self-efficacy, and DDKT/LDKT decisional balance, comparisons between the YPT and UC conditions by these three occasions will be made to determine if the intervention increases transplant knowledge, DDKT/LDKT self-efficacy, and DDKT/LDKT decisional balance scales. Finally, differences in the number of small steps toward LDKT and DDKT will be examined at these three time points.

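### Patients are randomized from scheduling records before they are called and consent, so the analysed arms are consenters rather than everyone randomized, and who consents could differ by arm

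*Protocol article*

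**What the plan says.** The order of events is in the article's section on patient recruitment, eligibility, randomization and retention. It begins with scheduling records: "The records of patients who have recently been scheduled for their evaluation day appointments will be obtained" from the clinic's database. These are then "randomized to a treatment group by a data manager, and uploaded into a patient recruitment and tracking database". The next step is the first patient contact: "Research staff will contact patients by telephone to be invited to participate in the study". Verbal consent, which also covers review of the medical record, comes at that stage.

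Other statements bear on the point:

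- Survey timepoints: the 40-minute baseline assessment is given to patients already in the YPT or UC condition.
- Recruitment section, on the database: "It will be continually updated by the study research coordinators and a data manager". The fields listed for it do not name the arm, and it is described as holding eligible patients.
- Recruitment section, on eligibility: one inclusion criterion is "self-identification as either White, Black or Hispanic race/ethnicity", and one exclusion is lack of consistent telephone access.
- Recruitment section and RCT overview: participation means three paid time points in UC and four in YPT, and only YPT includes coaching.
- Power and sample size: 450 per condition are to be recruited/consented. The Abstract instead says that 900 patients will be randomly assigned.
- Data management: records of patients who refuse or are never recruited are kept so that recruitment patterns can be reported.
- Statistical analyses: under intent-to-treat, "subjects will maintain their assignment to the treatment condition to which they were originally randomized". To look for selection, the "characteristics of patients who refuse to join the study or are never successfully contacted will be compared to those who do not".

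**The concern.** Randomization makes the arms comparable at the moment of allocation, over everyone allocated. Here contact, consent and the baseline survey all come after that moment, and patients lost at those steps leave the analysis. If the chance of being reached or of agreeing depends on the arm, and also on motivation to pursue living donation, the consenting arms differ before any coaching is given.

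This would reach every outcome, including the 8-month Action stage on which the trial is powered. Multiple imputation is no clear remedy. Patients who refuse have no survey data, and the record review for the 18-month outcomes rests on the consent that they did not give.

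**Working it through.** **1. Where the 450 is counted.** Power and sample size needs 300 per arm at 8 months with 66% retention: 300 / 0.66 = 455. With the 33% attrition given in the recruitment section, 300 / 0.67 = 448. The stated 450 agrees with both to within rounding. It is therefore a count of consented patients, who have already been randomized.

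**2. Consistency with the Abstract.** If a share c of randomized patients consents, 450 / c must be randomized per arm. The article gives no c. Assumed values give 450 / 0.8 = 563, 450 / 0.6 = 750 and 450 / 0.4 = 1,125 per arm. The 900 randomly assigned in the Abstract equals the 900 consented only if c = 1, yet the data management section expects refusals and patients never reached.

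**3. What differential consent could do.** All inputs except the 10% UC rate, the 300 per arm and the one-tailed 0.05 are assumptions. Suppose no treatment effect and half the patients motivated (m = 0.5). Action probability is a1 in motivated patients and a0 in the others, and consent is c1 and c0:

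Action rate among consenters = [m·c1·a1 + (1 − m)·c0·a0] / [m·c1 + (1 − m)·c0].

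Take a1 = 0.16, a0 = 0.04 and UC consent of 60% in both groups. UC rate = (0.048 + 0.012) / 0.60 = 10.0%.

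- YPT consent 60% / 50%: (0.048 + 0.010) / 0.55 = 10.5%, gap 0.5 points.
- YPT consent 60% / 40%: (0.048 + 0.008) / 0.50 = 11.2%, gap 1.2 points.
- YPT consent 70% / 50%: (0.056 + 0.010) / 0.60 = 11.0%, gap 1.0 point.

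With a1 = 0.18 and a0 = 0.02, the UC rate is again 10.0% (0.054 + 0.006 over 0.60). YPT consent of 70% / 40% gives (0.063 + 0.004) / 0.55 = 12.2%, gap 2.2 points, the largest tried.

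**4. Effect on the error rate.** With 300 per arm and gap d, the one-sided rejection probability is 1 − Φ[(1.645·SE0 − d) / SE1]. SE0 is the pooled and SE1 the unpooled standard error of the difference. For the 1.2-point gap, SE0 and SE1 are both 0.0251, so the argument is (0.0413 − 0.012) / 0.0251 = 1.17 and the probability is 12%. The 0.5, 1.0 and 2.2-point gaps give 8%, 11% and 21%. A two-sided 5% test rejects in about 6%, 8%, 7% and 14% for the gaps of 0.5, 1.2, 1.0 and 2.2 points.

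**5. Direction and detectability.** Exchanging the arms in the second case turns +1.2 into −1.2 points, so the sign depends on which patients are deterred from which arm. In the third case overall consent is 60% in both arms (0.35 + 0.25 in YPT, 0.30 + 0.30 in UC), yet a gap remains. Equal arm sizes at consent do not rule the problem out, and a comparison of refusers with joiners that pools the arms can miss it.

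**The case against.** The best defence is that two links in the chain are not stated. The article says that randomized records are uploaded. It does not say that callers see the arm, the listed database fields omit it, and masking by field is detail that a full protocol may hold. Nor does it say that the invitation reveals the arm to the patient, and the first coaching call is separate and comes after the baseline survey. The study flowchart is not shown. All of this stands: a reader might infer that recruiters work from a visible allocation, but the text does not establish it.

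A reader might also infer that no eligibility check precedes randomization, and that English, telephone access, wait-listing elsewhere and race/ethnicity can be learned only on the call. The article does not support that. "The REDCap recruitment database will include eligible patients" suggests some screening from records. Self-identified race/ethnicity and telephone access are the two items that would normally be confirmed at contact.

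The intent-to-treat objection is partly about words. Analysing consenters as assigned, whatever they receive, fits the article's own definition. What remains is that the set is not everyone randomized.

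The direction is also open. YPT asks more time, but it offers personal help and a fourth payment. Finally, baseline readiness is measured in both arms and refusers' records are kept, so imbalance could be partly seen and adjusted for. The article does not plan either by arm, though nothing prevents it.

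None of this changes the stated order, in which consent follows randomization.

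**Conclusion.** The concern holds as a risk built into a stated rule. Consent and the baseline survey follow allocation, no concealment is described, and the analysed set is consenters as assigned. The Abstract's 900 randomly assigned cannot equal the 900 recruited/consented if any randomized patient refuses.

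Whether selection differs by arm cannot be known from the article. The gaps of 0.5 to 2.2 points rest wholly on assumed motivation and consent patterns. They are 5% to 22% of the planned 10-point difference, so they would not by themselves create an effect of the planned size. They would matter for the validity of the test, with one-sided error of about 8% to 21% in place of 5%. Those error rates assume 300 analysed per arm and no baseline adjustment. The point merits action because this selection cannot be reliably undone in the analysis, while preventing it is cheap.

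**What to change.** - **New patients:** release the allocation only after eligibility is confirmed, verbal consent is given and the baseline survey is complete. The first YPT coaching call is already separate and typically within 14 days after that survey, so there is room for this step.
- **Patients randomized but not yet called:** keep the arm hidden from callers and out of the invitation until the baseline survey is locked.
- **Patients already enrolled under the present order:** report numbers randomized, contacted, eligible, refused and consented by arm, using the retained recruitment records. Compare refusers and baseline characteristics by arm. Adjust the 8-month comparison for baseline LDKT readiness.
- **Wording:** for these patients, describe the analysis set as consented patients analysed as assigned, and reconcile the Abstract's 900 randomly assigned with the 900 recruited/consented.

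The cost is a small REDCap and call-script change and a short amendment. Baseline adjustment reduces measured imbalance only, so it does not replace the change in order. Stratifying by race/ethnicity is a separate option that this fix does not need.

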### Survey timepoints

To begin the trial, we will conduct a 40-minute assessment of patients in the YPT and UC conditions to measure their demographic and clinical characteristics, any socioeconomic barriers to transplant, as well as their baseline DDKT and LDKT knowledge, decision-making, readiness, and self-efficacy. Upon beginning evaluation approximately 3–5 weeks later, patients in the YPT condition will repeat components of the survey during a 10-minute assessment. Four and 8 months later, patients in both conditions will complete two more 15-minute surveys to assess how their knowledge, decision-making, and behavior are changing over time. During the final 8-month interview, we also will ask patients questions regarding the cultural competency of their medical providers and other process measures including whether they had made an informed decision as to whether or not pursue DDKT or LDKT, and the overall helpfulness of the education they received.

For patients in the UC education condition, no additional education or coaching will occur after these surveys are administered. Patients in the UC education condition will receive a $10 gift card and a letter of thanks in the mail after each time point. Patients in the YPT condition will receive additional education and tailored coaching, as discussed next.

### YPT baseline education and coaching

Typically within 14 days post-baseline survey, patients randomized to YPT will have a separate 25-minute baseline coaching telephone call. During this call, as prompted by bulleted coaching recommendations generated by the YPT computerized program, the coach will discuss the most relevant content to support each patient in completing transplant evaluation successfully and pursuing LDKT. Immediately after the call, the coach will mail each patient a folder containing the informed consent documents, an individually-tailored feedback report generated from their answers to the baseline survey, print DDKT and LDKT educational resources, including a *Community Resource Guide*, and a $10 gift card.

### YPT evaluation day education and coaching

On evaluation day, 3 to 5 weeks after baseline, patients in the YPT intervention condition will be taken to a private area in the hospital where they will be reassessed to see how their transplant decision-making is changing. Then, the coach will provide 10-minutes of feedback based on any changes in readiness, confidence, and perceived benefits or concerns that have occurred since the initial assessment. Since the focus of this meeting is LDKT, patients also will watch a 10-minute LDKT video appropriate for their level of readiness and a discussion will be held about small steps they could take that honor their stage of readiness to further explore or pursue LDKT (20 minutes total time). At the end of the session, the coach will give the patient a second folder including an individually-tailored feedback report, print educational materials about LDKT, including an *Explore Transplant* video, educational resources to share with their family members and friends, and a $10 gift card. This meeting will take 30 minutes (20 minutes of coaching and 10 minutes for survey assessment).

### YPT 4- and 8-month education and coaching

During two additional telephone assessments at 4- and 8-months following baseline, patients will be resurveyed (15–20 minutes) to see how their decision-making and behavior is changing and, in the YPT education condition only, surveyed at 8 months about YPT’s helpfulness. Tailored coaching (15 minutes) will be given by telephone and individual feedback reports and $10 gift cards mailed following the phone call.

### YPT coaching fidelity

Throughout the intervention, the coaches will participate in weekly calls with a clinical psychologist, [name], to discuss questions and continue to improve the tailored coaching process. Coaches administering the YPT intervention will be assessed for fidelity using a standard rubric [47]. All patient interviews will be audio recorded with the patient’s consent. For each coach, the first 10 calls will be reviewed to ensure competency, then, afterwards, a randomly selected 10% of their calls will be reviewed by two raters and checked to see if the content and dose of the intervention has been delivered consistently, per protocol. Coaches administering the intervention and coaching to the intervention group will be rated on: 1) their standardized interviewing technique; 2) the consistency of coaching to TTM principles (e.g., effective tailoring to stage of readiness); 3) effective delivery of additional trial components (e.g., addresses socioeconomic status barriers to transplant, cultural competency); and 4) effective communication skills and rapport. Coaches scoring below a minimum threshold will be required to undergo further training before continuing with the trial.

### Outcome measures

#### LDKT and DDKT readiness

Using validated measures [44, 45], patients will be asked how ready they are to get a DDKT by reporting whether they are “not considering getting a DDKT in the next six months” (Precontemplation), “considering getting a DDKT in the next six months” (Contemplation), “preparing to get a DDKT in the next 30 days” (Preparation), “undergoing evaluation to get a DDKT” (Action) or “listed and waiting to get a DDKT” (Maintenance) [44]. Patients will also be asked how ready they are to pursue LDKT and to rate whether they are “not considering taking actions in the next six months to pursue LDKT” (Precontemplation), “considering taking actions in the next six months to pursue LDKT” (Contemplation), “preparing to take actions in the next 30 days to pursue LDKT” (Preparation), or “taking actions to pursue LDKT” (Action) [45].

#### Small steps toward LDKT and DDKT

To assess their steps toward transplant, patients will be asked to respond whether they have “Already done”, “Are planning to do”, or “Don’t plan to do” a list of actions related to LDKT [45] and DDKT [44]. Examples of steps toward LDKT include “Read information/watch videos about getting a living donor transplant” and “Ask potential donors to be tested”, while examples of steps toward DDKT include “Share educational materials about deceased donation with people in your life” and “Follow-up with the transplant coordinator until transplant evaluation is complete”.

#### Decisional balance and self-efficacy

Decisional Balance measures will assess how patients weigh the relative importance of possible LDKT and DDKT positive and negative outcomes (e.g., “My living donor will feel good seeing my health improve”). Patients will be asked to rate the importance of each statement on a 5-point scale ranging from, (1) “Not important” to (5) “Extremely important” [44, 45]. The Self-Efficacy scale measures the confidence an individual has in his/her ability to pursue transplant in a wide variety of challenging situations (e.g., “If your friends and family were unsupportive of you getting a transplant”) on a scale from (1) “Not at all confident” to (5) “Completely confident” [44, 45].

#### Transplant knowledge

Patients will be asked 11 true/false and 8 multiple choice questions to determine their level of knowledge regarding basic facts, advantages, risks and outcomes of DDKT and LDKT (e.g., “Patients older than 80 years can receive transplants”; “Compared to transplants from donors who have died, how long do transplants from living donors last?”) [10]. A measure of transplant knowledge is then created by summing the number of correct answers to the questions.

#### Final transplant outcome

Finally, patients’ electronic medical records at UCLA and data from the Scientific Registry for Transplant Recipients (SRTR) will be reviewed 18 months post-baseline to create a final study outcome for each patient. At the study’s conclusion, the patient will be coded as to: 1) be waitlisted for a DDKT; 2) have received a DDKT; 3) have received a LDKT; 4) have been determined to be medically ineligible for transplant; 5) have died; or 6) have dropped out of evaluation.

### Predictors and covariates

#### Demographic, clinical and cultural factors

Many other patient characteristics will be assessed including age, sex, race/ethnicity, dialysis status (on or off dialysis; if on, hemodialysis or peritoneal), patient comorbidities (e.g., the presence of diabetes, hypertension, polycystic kidney disease) and validated measures of health-related quality of life, including the Medical Outcomes Study (MOS) SF-12v2 [48] and a patient-reported Karnofsky rating of health status [49]. To examine how other known causes for health disparities in transplant affect key outcomes we will also assess medical mistrust using the Medical Mistrust Index, a validated scale that assesses patients’ agreement with 7-items about their trust of health care organizations (E.g., “Patients have sometimes been deceived or misled by health care organizations”) [29, 50].

